#### Patients

On onsite recruitment days, participating clinics placed signs in registration areas that asked, 'Do you want to improve your emotional health and possibly earn up to $75?' The signs also specified which clinicians were participating in the study. During registration, patients were given a card that informed them their clinician was participating in a study to improve emotional health in African Americans, and they might be approached by a research assistant to ask if they were willing to participate. The patient could return the card to the receptionist if the patient was not African-American and/or did not wish to be approached. Those who agreed to be screened completed the procedures in a private area of the clinic. The research assistant described the study and obtained verbal consent to complete a 10-minute depression screening interview in a private room. Patients who were positive on the first-stage depression screen completed full written study consent, and a research assistant arranged for the patient's medical visit to be audio taped.

Patients who screened positive for depressive symptoms in clinical sites were called at home within two weeks of their onsite screening to complete the second-stage screen (to determine whether they had a diagnosis of MDD by the Composite International Diagnostic Interview, or CIDI) with a 40-minute telephone baseline interview [29,30]. If they met diagnostic criteria, they were randomized according to their clinician's intervention assignment and told to expect a phone call from a depression care manager within a few days; interviewers also obtained respondents' consent to be called for 30-minute follow-up interviews at 6, 12, and 18 months from the baseline interview.

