#### Patient interventions

The standard and patient-centered patient interventions were both designed to incorporate state-of-the-art strategies that have been proven to enhance the quality of care for depression in primary care settings. Each intervention involved extensive one-on-one follow-up with a Depression Case Manager (DCM) to assess patients' depression status and to encourage adherence to recommended treatments and exposure to educational materials. Both DCMs were social workers with clinical experience; the standard DCM was a Caucasian woman, and the patient-centered DCM was an African-American woman.

The format and schedule for DCM contact were standardized across both interventions. Enrolled patients were contacted by their DCM within a week of the baseline telephone interview to schedule a 45-minute telephone conversation. Follow-up calls at one week, two weeks, and four to six weeks assessed each patient's depression level measured by the Patient Health Questionnaire (PHQ-9) score [40]. Symptomatic patients in the acute phase received weekly calls, while asymptomatic patients in the continuation and maintenance phases were called every eight and 12 weeks, respectively. Each DCM was also available to her patients by telephone as needed throughout the duration of the 12-month intervention.

The common goals of the standard and patient-centered DCMs were to provide needs assessment (five core areas for the standard DCM, 11 core areas for the patient-centered DCM), education, and activation messages to patients (Table 1). In addition to core areas, the needs assessment touched on active coping strategies, social stressors, and social support. To increase the efficiency and effectiveness of depression care, during every follow-up call each DCM monitored symptoms, functional status, and general health of her patients. In addition, each DCM reviewed the psychotherapy, medication, and/or alternative treatment plan developed by the patient and his or her primary care clinician. A report of relevant information was prepared for the patient, primary care clinician, and/or mental health specialist after each contact.

**Table 1 T1:** Features of the BRIDGE study patient intervention

Data collected/delivered	Standard intervention	Patient-centered intervention
Needs assessment (five core assessment areas)	X	

Patient-centered needs assessment^1 ^(11 core assessment areas)[41]		X

Education and Activation	X	X

Social support/informal counseling	X	X

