**Questionnaires**				

Sociodemographics	X		X	X
Age, sex, race/ethnicity, education, income, employment^1^, health insurance^1^, financial stress^¶^				

Attitudes, beliefs, and other behavioral measures	X	X	X	X
Trust in health professionals, preferred role in decision-making, depression treatment preferences, spirituality, respect, perceived involvement in care^2^, racial identity, social support, life events				

Health Status	X	X	X	X
Physical and mental, measured by MOS-SF12, CIDI^3 ^&ES-D, psychiatric co-morbidity^4^, disability days				
Healthcare Utilization	X	X	X	X
Mental healthcare utilization (receipt of antidepressant medication and/or counseling) General healthcare utilization (emergency room visits and hospitalizations)				
Healthcare Process	X	X	X	X
PDM with providers, visit-specific and overall satisfaction, satisfaction with case manager^5^, ratings of depression care management and intervention materials^6^				

**Audiotapes **(patient-provider communication)^7^	X			

CIDI = Composite International Diagnostic Interview, Depression Scale, CES-D = Center for Epidemiologic Studies Depression Scale, PDM = participatory decision making; ^1^measured at 12 and 18 months; ^2^measured only at 18 months; ^3^not measured at six months; ^4^Substance abuse, panic attacks, anxiety, and traumatic events; ^5^measured only at six and 12 months; ^6^measured only at 12 months only; ^7^collected at enrollment visit and after primary care provider intervention.

One modification to the original study protocol was made shortly after the 12-month follow-up was complete. Because the pattern of improvement differed between intervention groups at six months and 12 months of follow-up, a decision was made to extend follow-up to one additional interview at 18 months, and IRB approval was obtained to re-contact study patients. However, because outcomes assessors at 18 months were not blinded to intervention assignment, depression status at 12 months remains the study's primary outcome.

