The data on outcome variables fall into two broad categories: continuous variables, such as depressive symptom score (CES-D) [48] and functional status scores (MOS SF-12) [49], and dichotomous variables, such as depression remission status and receipt of guideline-concordant treatment. The primary ITT analyses are designed as regression modeling using patients as the unit of analysis, with each regression model structured to have a parameter designated for each visit where the outcome of the model was scheduled to be assessed, separately for each intervention group, so that the mean model is fully saturated for the intervention by visit parametrization. This parametrization allows estimation of mean differences observed within each intervention group betweeen baseline and a given follow-up visit for a continuous outcome, and odds ratios of having the outcome event at a given follow-up versus the baseline visit within each intervention group for a binary outcome, after adjusting for other covariates in the model. The evalution of patient-centered intervention effects will be conducted by testing the significance of difference of the adjusted mean differences, or the ratio of adjusted odds ratios, of a given follow-up versus the baseline visit between the intervention groups. The primary testing contrast is the baseline to 12-month change in outcomes between intervention groups; the models can easily accommodate additional data obtained by extending the follow-up to 18 months.

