#### Baseline characteristics of patients

Research assistants approached 1,486 patients for eligibility in waiting rooms between October 2005 and August 2006; 613 refused to complete in-person screening and 642 were determined to be ineligible by the first-stage screener (*e.g*. 457 were not depressed, 68 were positive for alcohol or drug abuse by the CAGE AID [51,52], and 46 were currently seeing a mental health specialist). Of the 231 patients eligible for the second-stage screen, conducted by telephone, 35 refused to complete it when called, 22 were unable to be reached to confirm their eligibility, and 42 were categorized as ineligible by the second-stage screen (CIDI). (Figure 3) Table 6 shows baseline characteristics of the 132 patients enrolled in the study. These patients are 46.4 years on average; 80% are women and 100% are African-American (4% also report being of Hispanic ethnicity). Forty-nine percent are high school graduates. The average annual household income is $41,393; however, 28% find it very difficult to pay their monthly bills. Fifty-eight percent are employed, and 89% have health insurance. The mean scores on the CES-D, MCS-12, and PCS-12 at baseline are 29.84, 36.18, and 42.12, respectively. Fifty-six percent of the sample reported having to take at least one disability day in the preceding two weeks.

**Table 6 T6:** BRIDGE study: Baseline demographic and clinical characteristics for 132 African American patients

Characteristic	Number of patients (%)	Mean (standard deviation)
Age, years, mean (SD)		46.4 (11.1)
Gender, female	105 (79.6)	
Ethnicity		
Hispanic	5 (3.8)	
Non-Hispanic	127 (96.2)	
Marital status, married	36 (27.3)	
Education		
< High school graduate	12 (9.0)	
High school	65 (49.2)	
Some college	50 (37.9)	
College graduate	5 (3.8)	
Annual household income		$41,393 ($26,840)
Employed		
Full-time/part-time	77 (58.3)	
Other^1^	55 (41.7)	
Healthcare insurance Payer	117 (88.6)	
Medicaid	21 (18.0)	
Medicare	25 (21.4)	
Other	82 (70.1)	
CES-D score		29.84 (14.09)
MOS-SF-12, physical component		42.13 (13.2)
MOS-SF-12, mental component		36.18 (12.6)
Comorbid medical condition		
Diabetes	46 (34.9)	
Hypertension	72 (54.6)	
Trouble breathing	33 (25.0)	
Back problems	40 (30.3)	
Arthritis/rheumatism	56 (42.4)	
Had one or more disability days in last two weeks	74 (56.1)	
Taking antidepressant medication	101 (76.5)	
Treated for depression at most recent visit	65 (49.2)	

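### The article conflicts on when the 18-month interview was planned; if it was added after 12-month follow-up, the earliest enrollees were already well past 18 months

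*Protocol article*

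**What the plan says.** Two sections of the protocol article describe the origin of the 18-month interview differently.

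- **Recruitment strategies, Patients.** Interviewers at the baseline telephone interview obtained "consent to be called for 30-minute follow-up interviews at 6, 12, and 18 months from the baseline interview". On this account the 18-month call was foreseen from the start.
- **Data collection at baseline and over follow-up, text after Table 4.** "One modification to the original study protocol was made shortly after the 12-month follow-up was complete". The stated reason is that the groups' improvement patterns at six and 12 months differed, and so "a decision was made to extend follow-up to one additional interview at 18 months, and IRB approval was obtained to re-contact study patients". The same paragraph keeps 12 months as the primary time point because the 18-month assessors were not masked.

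The dates are in Baseline characteristics of patients: "Research assistants approached 1,486 patients for eligibility in waiting rooms between October 2005 and August 2006".

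The Main outcome measures and statistical analysis plan section gives each scheduled visit its own parameter in each arm, names baseline to 12 months as the primary contrast, and adds that "the models can easily accommodate additional data obtained by extending the follow-up to 18 months". The Abstract includes eighteen months in the main hypothesis. Specific aims two and three stop at 12 months.

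**The concern.** The enrolment period was longer than six months. An interview conceived only after the last patient's 12-month assessment therefore comes too late to reach the earliest patients at 18 months. If the account after Table 4 is right, the visit called 18 months holds a mixture of times, and each patient's time depends on when that patient enrolled.

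This matters for interpretation because the case managers' support ran "throughout the duration of the 12-month intervention". A later assessment measures whether benefit persists after support ends. At 18 months a patient is 6 months past the end of support; at 21 to 24 months, 9 to 12 months past it. A result reported as an effect at 18 months would not describe one defined interval. The article discloses that the assessors were unmasked, but nowhere mentions the timing.

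**Working it through.** **Inputs**

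- Approach window: October 2005 to August 2006. Days of the month are not given, so I take an outer reading (1 October to 31 August, 334 days, about 11 months), an inner reading (31 October to 1 August, 274 days, about 9 months) and a mid-month reading (304 days, about 10 months).
- Lag to baseline: screen-positive patients were "called at home within two weeks of their onsite screening to complete the second-stage screen", so 0 to 14 days. Follow-up months count from the baseline interview.
- Earliest decision: after 12-month follow-up had finished, which I read as finished for all patients.
- Delay *d* for the decision and IRB approval: not stated. Assumed 0 to 1 month, with 2 to 3 months as an extension.

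**Do all patients fall in the window?** 1,486 − 613 − 642 = 231, and 231 − 35 − 22 − 42 = 132. This matches the article: "Table 6 shows baseline characteristics of the 132 patients enrolled in the study". The flow closes, so all 132 come from that window.

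**Formulas**, with *L* the accrual length in months:

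- earliest re-contact = last baseline + 12 + *d*
- first patient's time since baseline at that date = *L* + 12 + *d*
- share already past 18 months under even accrual = (*L* − 6 + *d*) / *L*

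The share is above zero for any *L* over 6 months, even with no delay.

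**Results** (shares counted in days)

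| Reading of window | *d* (months) | Earliest re-contact | Past 18 months | Of 132 | First patient at |
|---|---|---|---|---|---|
| Outer | 0 | 31 Aug 2007 | 151/334 = 45% | 60 | 23 months |
| Outer | 1 | 30 Sep 2007 | 181/334 = 54% | 72 | 24 months |
| Inner | 0 | 1 Aug 2007 | 91/274 = 33% | 44 | 21 months |
| Inner | 1 | 31 Aug 2007 | 121/274 = 44% | 58 | 22 months |
| Mid-month | 0 | 15 Aug 2007 | 121/304 = 40% | 53 | 22 months |
| Mid-month | 1 | 14 Sep 2007 | 151/304 = 50% | 66 | 23 months |

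A two-week lag common to all patients moves the calendar dates (31 August becomes 14 September 2007) and leaves the shares and months unchanged. If the lag differs between the first and last patient, the months move by at most half a month. On the outer reading, a delay of 2 to 3 months gives 63 to 72% past 18 months and a first patient at 25 to 26 months.

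**Accrual pattern.** Monthly accrual is not reported. At the outer, zero-delay cut (5/11 of the window), strongly back-loaded accrual gives (5/11)² = 21%, and strongly front-loaded accrual gives 1 − (6/11)² = 70%.

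**Order of events.** The first patients reached 18 months between April and mid-May 2007. The decision could not have come before August 2007.

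**The case against.** The strongest reply is that the recruitment section may be the accurate one. If patients agreed at baseline to an 18-month call, interviews could have been made on time. The article gives no decision date, IRB date or interview date that would settle it. This stands: the timing conclusion is conditional on the account after Table 4.

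A reader might infer that half the patients cannot have been interviewed at 18 months. The documents do not support that as fact. It presumes one of two conflicting accounts, and the share rests on an accrual pattern that is not reported.

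A reader might also infer that the arms are compared unfairly. Nothing shows that enrolment dates differed by arm. Randomization was stratified by site in small blocks, site and clinician characteristics are covariates, and re-contact is described as a single study-wide step. A pooled late visit is still a comparison of the randomized groups. What suffers is its label and its reading as durability at a set time.

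The Randomization section mentions permission for contact over 12 months. That may be a separate consent step at the screening visit, so I do not rely on it as a further contradiction.

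Finally, visit windows are commonly left to an analysis plan that is not shown. That is fair for the windows themselves, but it does not remove a conflict between two stated accounts, or between a stated time point and the stated dates.

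**Conclusion.** The point holds in conditional form. The two accounts of when the 18-month interview was planned conflict. If the interview was added after all patients had finished 12-month follow-up, the earliest enrollees were about 21 to 24 months from baseline when re-contact could begin. That result needs only the stated dates, the natural reading of complete follow-up, and a delay of 0 to 1 month; a longer delay makes it later.

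The share affected is softer: about one third to one half (33 to 54%) under assumed even accrual and 0 to 1 month of delay, and about 20 to 70% under other accrual patterns. Later enrollees, at 12 to 13 months on those dates, could still be interviewed on time. The visit parameter would therefore mix about 18 months with 21–24 months or more.

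The consequence is confined to the 18-month comparison, an unmasked late extension that the Abstract nevertheless places in the main hypothesis. It does not follow that the comparison is worthless, that the arms are biased, or that the primary 12-month result is affected.

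**What to change.** 1. Reconcile the Patients recruitment section with the text after Table 4: state whether the 18-month interview was planned and consented to at baseline or added later, and give the dates of the decision and IRB approval.
2. If it was added later, label the assessment as extended post-intervention follow-up, and align the eighteen-month wording in the Abstract's hypothesis.
3. Report actual months since baseline at that interview, by arm.
4. Before any statement about an effect at 18 months, add a sensitivity analysis that uses actual time since baseline, or one limited to interviews near 18 months. Actual time is preferable as the main check, because a restriction would keep mostly late enrollees and could drop a third to a half of the sample.

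This should need only the interview dates and no new data collection. The cost is a little more analysis work and less precision for any strictly 18-month estimate.

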#### Main outcome measures and statistical analysis plan

Randomly assigned intervention group (standard versus patient-centered) is the main independent variable for intent-to-treat (ITT) analyses. Clinic site is a stratification variable for randomization and is expected to be balanced across intervention groups by design. The primary outcome variable is change in depression symptom severity, upon which we base the sample size evaluation to ensure proper statistical power. Descriptive statistics will be used to describe patient and clinician characteristics at baseline. The comparability of clinician characteristics between intervention groups will be determined for sociodemographic data as well as pre-intervention measures of training, attitudes, management of depression, and communication style. Comparability of patient characteristics between intervention groups will be assessed with regard to pre-intervention sociodemographics, depression level, health status measures, and other key variables. Variables found to be unbalanced between intervention groups will be adjusted for in all ITT analyses. Adherence to the intervention (*e.g*. number of intervention visits kept) will be considered as a covariate in subsidiary, on-treatment analyses.

The data on outcome variables fall into two broad categories: continuous variables, such as depressive symptom score (CES-D) [48] and functional status scores (MOS SF-12) [49], and dichotomous variables, such as depression remission status and receipt of guideline-concordant treatment. The primary ITT analyses are designed as regression modeling using patients as the unit of analysis, with each regression model structured to have a parameter designated for each visit where the outcome of the model was scheduled to be assessed, separately for each intervention group, so that the mean model is fully saturated for the intervention by visit parametrization. This parametrization allows estimation of mean differences observed within each intervention group betweeen baseline and a given follow-up visit for a continuous outcome, and odds ratios of having the outcome event at a given follow-up versus the baseline visit within each intervention group for a binary outcome, after adjusting for other covariates in the model. The evalution of patient-centered intervention effects will be conducted by testing the significance of difference of the adjusted mean differences, or the ratio of adjusted odds ratios, of a given follow-up versus the baseline visit between the intervention groups. The primary testing contrast is the baseline to 12-month change in outcomes between intervention groups; the models can easily accommodate additional data obtained by extending the follow-up to 18 months.

Site and clinician characteristics are included as covariates in all regression models to account for potential patient outcome clustering within clinical sites and/or clinicians. To account for longitudinal correlations between outcome assessed over time within patients, mixed effects modeling appraches with unstructured correlation matrix are used whenever possible. Robust estimation is used for statistical inferences. The likelihood approach underlying the proposed mixed effects modeling would produce valid statistical inferences with missing data if the missing mechanism is Missing at Random (MAR) and the proposed mean and correlation models are correct. We thus anchor our ITT analyses on mean models with fully saturated visit by intervention parametrization plus all the covariates as necessary, paired with an unstructured correlation model to develop valid statistical inferences under MAR. We then conduct sensitivity analyses through multiple imputation under plausible missing scenarios that are non-MAR to examine the robustness of our inferences under such situations.

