#### Data collection at baseline and over follow-up

In addition to the main outcome and process measures, baseline data were collected to describe the characteristics of study subjects and compare these characteristics between the intervention groups assigned by randomization. While the intervention status is the main predictor variable, other factors known to be predictors of depression (*e.g*., social support) and factors that might explain why the intervention did or did not work (*e.g*., clinician and patient attitudes regarding treatment) were collected. In general, we selected instruments that are brief, have been used successfully in primary care settings, and are reliable and valid in primary care clinicians and African Americans. We also collected detailed data on racial identity and other attitudes, beliefs, and experiences that might identify intra-ethnic group differences and help determine the study's external validity. We conducted telephone interviews to measure patients' depression status, attitudes regarding treatment, use of health services and experiences of care, and reactions to the interventions at six and 12 months of follow-up. Table 3 shows the variables collected from individual clinicians at baseline (pre-intervention), immediately after their in-person intervention contacts (post-intervention), and at the end of the study. Table 4 shows socio-demographic and behavioral variables, clinical measures, and health service utilization patterns collected from patients at baseline and over follow-up.

**Table 3 T3:** Schedule of data collected from primary care clinicians in the BRIDGE study

Overall data collection	Pre intervention	Post intervention
Demographics (age, gender, race, ethnicity, place of birth, residency training, board certification status, practice experience)	X	

Specialty (internal medicine or family medicine)	X	

Previous communication skills CME training	X	X

Previous mental health CME training	X	X

Readiness to change behavior re: management of depression	X	

Knowledge, attitudes, self-efficacy re: managing depression	X	

Attitudes about race^1^	X	X

Self-reported communication and PDM style	X	

Job stress and satisfaction	X	

Self-efficacy in managing adherence problems, depression, and patients from socially and culturally diverse backgrounds	X	X

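### Covariates enter every ITT model because they differ by arm, from an open list that could include measures taken after clinician training; they should be named on prognostic grounds

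*Protocol article*

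**What the plan says.** All of the following is in the Protocol article, mostly under Main outcome measures and statistical analysis plan.

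- The rule: "Variables found to be unbalanced between intervention groups will be adjusted for in all ITT analyses".
- The patient variables to be compared are "pre-intervention sociodemographics, depression level, health status measures, and other key variables". For clinicians they are sociodemographics and "pre-intervention measures of training, attitudes, management of depression, and communication style".
- The fixed part of the model: "Site and clinician characteristics are included as covariates in all regression models". The clinician characteristics are not named.
- The open part: "mean models with fully saturated visit by intervention parametrization plus all the covariates as necessary".
- The target: "The primary testing contrast is the baseline to 12-month change in outcomes between intervention groups", from a model with a separate mean for each arm at each visit.

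The section Data collection at baseline and over follow-up says that the study also collected "other factors known to be predictors of depression", with social support as its example. No sentence ties those predictors to the primary model.

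**The concern.** Difference between arms is a poor reason to adjust. It says nothing about whether a variable predicts CES-D or remission. It brings in variables that differ but do not matter, and it gives no assured place to a strong predictor that happens to look similar in the two arms. The closing item of the patient list has no boundary, so the adjusted estimate is not defined until someone decides what counts as unbalanced.

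Two features of this trial make that matter more. First, the last paragraph of Data collection at baseline and over follow-up says that follow-up was extended to 18 months because improvement differed between the groups at six and 12 months. Between-group patterns had therefore been seen while the rule was still to be applied. Second, clinicians were randomised before their patients were recruited. Some measures labelled as baseline for the patient may then have been taken after the clinician was trained. An arm difference in such a measure can be an effect of the intervention, and adjusting for it removes part of what the trial is meant to estimate.

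**Working it through.** The plan attaches no figure to this rule, so there is none to reproduce. The 3.6-point detectable difference under Sample size considerations does not depend on it.

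**1. Effect on the primary continuous contrast.** Write the mean for patient i in arm g at visit t as m(g,t) + b·x(i), where x is a baseline covariate entered as a main effect. The patient's expected change from baseline to 12 months is m(g,12) − m(g,0), and the term b·x(i) drops out. A numerical check with 132 patients, complete data and a covariate shifted by 0.5 SD between arms gave:
- no covariate: −4.726
- covariate as main effect: −4.726
- covariate interacting with visit: −5.610

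So the rule alters this contrast only through covariate-by-visit terms or missing data. The plan does not say whether covariates interact with visit, and its sample size allows for 15% dropout. A separate check with about 15% covariate-dependent dropout and a prognostic covariate imbalanced by 0.4 SD moved the estimate by 0.11 points on average, against a standard error of about 1.8. For remission and guideline-concordant care the models estimate odds ratios, and an adjusted odds ratio depends on which covariates are in the model.

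**2. Type I error and power where covariates do act on change.** Assumptions, none from the plan: 132 patients in equal arms, no clustering, 20 independent baseline variables of which three explain 30% of the variance of change (SD 10), unbalanced meaning p<0.05, and 6,000 runs.
- Flags expected by chance: 20 × 0.05 = 1.0. Probability of at least one: 1 − 0.95^20 = 64%.
- Type I error: 4.1% under the rule, 5.4% with the three predictors named in advance (5% within simulation error).
- Type I error if an analyst could pick the better of the adjusted and unadjusted results: about 5.8%.
- Power at a true difference of 5 points: 82% under the rule, 82% unadjusted, 92% with the three predictors named in advance.

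**3. Timing of patient measures.** These statements are set side by side:
- Randomization: clinicians were assigned first, and patients took their clinician's assignment.
- Discussion: randomisation could not wait for a first patient, partly because of the time needed to deliver the clinician interventions.
- Table 3: audiotapes with depressed patients are marked only in the post-intervention column.
- Table 4, footnote 7: those audiotapes are tied to the enrollment visit and to a time after the clinician intervention.
- Recruitment strategies, Patients: the telephone baseline interview comes within two weeks after on-site screening.

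Together they imply that enrollment-visit data generally follow clinician training. Table 4's enrollment column includes trust, participatory decision-making and satisfaction. Specific aim three treats satisfaction as an outcome.

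**4. Possible size of adjusting for such a measure.** Same assumptions as step 2, except that training shifts one of the three predictors by 0.5 SD and that predictor carries part of the effect. The true total is 3 + 0.5 × 3.162 = 4.58 points. The mean estimate was 4.57 unadjusted and 3.16 under the rule, and power fell from 74% to 43%. Naming that measure in advance gave 3.01, so naming is not enough: the covariate must also be one that training cannot change.

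**The case against.** The strongest reply has five parts.

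- *The p-value is not invalidated.* A reader might infer that choosing covariates by imbalance makes the nominal p-value and interval invalid. The simulation does not support that. Selection uses baseline data, and type I error was about 4%. This stands.
- *The primary contrast is largely protected.* With complete data, main-effect covariates cancel. This also stands. The power and mediator figures in steps 2 and 4 apply only where covariates act on change itself.
- *Imbalance here need not be chance.* Patients were recruited after clinicians were randomised, some clinicians contributed none, and the arms had 15 and 21 clinicians. The Discussion recognises this and cites adjustment or propensity-score methods, with sensitivity analyses. This is a fair reason to look at imbalance. It does not make an open screen the right basis for the main model.
- *The screened measures are described as pre-intervention, and other covariates may be added.* True. Trust, satisfaction and participatory decision-making could enter only through the open last item of the patient list, and their post-training timing is an inference. Nor does the rule bar strong predictors: site and clinician characteristics are always in, and others may be added as needed.
- *Thresholds and covariate names belong in an SAP.* Their absence is not the point. The article states the criterion itself, which is imbalance.

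A reader might also count 30 or 45 characteristics in the tables and infer a 79% or 90% chance of a spurious flag, or infer that only 17 between-clinician degrees of freedom remain. The first needs a 5% test and independent variables. The second needs a cluster-level analysis. The article specifies none of these. It takes patients as the unit of analysis, with robust inference.

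**Conclusion.** The rule should be replaced, but it is not an error that invalidates the primary test. It selects covariates on the wrong criterion from an unbounded list. Its effect on the CES-D change contrast is nil with complete data and main effects only, and was small in the one dropout scenario checked. It can be larger for the binary outcomes or with covariate-by-visit terms. The costs are an estimate not defined in advance, room for choice after between-group patterns were known, and power forgone (82% against 92% under the stated assumptions).

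Adjusting away part of the intervention effect is a possibility, not something the article commits to. It rests on the timing inference and on such measures being counted among the other key variables. The fall from 4.57 to 3.16 points shows only how large the loss could be under assumed inputs. Nothing in the article shows that covariates were in fact chosen with outcomes in view.

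**What to change.** Replace the rule with a covariate set named on prognostic grounds and not alterable by clinician training:

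- site, the stratification factor;
- the clinician characteristics already promised for every model, now named;
- one or two patient predictors, such as social support (the plan's own example) or age.

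Keep baseline CES-D as a response in the saturated visit model. It is already there and should not be added again as a covariate, although depression level is on the list to be compared. State whether covariates interact with visit. Because between-group patterns have been seen, have the set chosen without reference to outcome by arm, and record that.

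Report the baseline tables descriptively. Because recruitment after randomisation can produce systematic imbalance, report an imbalance-adjusted model as a sensitivity analysis, excluding measures taken after exposure to a trained clinician.

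The cost is a change of wording and no new data. The downside is that an imbalance in an unlisted variable is dealt with only in the sensitivity analysis.
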